## Abstract

**Background:**

Regular participation in physical activity by people with cystic fibrosis (CF) promotes positive clinical and health outcomes including reduced rate of decline in lung function, fewer hospitalizations and greater wellbeing. However adherence to exercise and activity programs is low, in part due to the substantial daily therapy burden for young people with CF. Strict infection control requirements limit the role of group exercise programs that are commonly used in other clinical groups. Investigation of methods to promote physical activity in this group has been limited. The Active Online Physical Activity in Cystic fibrosis Trial (ActionPACT) is an assessor-blinded, multi-centre, randomized controlled trial designed to compare the efficacy of a novel web-based program (ActivOnline) compared to usual care in promoting physical activity participation in adolescents and young adults with CF.

**Methods:**

Adolescents and young adults with CF will be recruited on discharge from hospital for a respiratory exacerbation. Participants randomized to the intervention group will have access to a web-based physical activity platform for the 12-week intervention period. ActivOnline allows users to track their physical activity, set goals, and self-monitor progress. All participants in both groups will be provided with standardised information regarding general physical activity recommendations for adolescents and young adults.

Outcomes will be assessed by a blinded assessor at baseline, after completion of the intervention, and at 3-months followup. Healthcare utilization will be assessed at 12 months from intervention completion. The primary outcome is change in moderate-to-vigorous physical activity participation measured objectively by accelerometry. Secondary outcomes include aerobic fitness, health-related quality of life, anxiety and depression and sleep quality.

**Discussion:**

This trial will establish whether a web-based application can improve physical activity participation more effectively than usual care in the period following hospitalization for a respiratory exacerbation. The web-based application under investigation can be made readily and widely available to all individuals with CF, to support physical activity and exercise participation at a time and location of the user’s choosing, regardless of microbiological status.

**Trial registration:**

Clinical trial registered on July 13, 2017 with the Australian and New Zealand Clinical Trials Register at (ACTRN12617001009303).

## Background

Cystic Fibrosis (CF) is a complex, multi-system inherited disorder. This progressive disorder is commonly characterised by chronic suppurative lung disease, including bronchiectasis, progressing to respiratory failure [1]. People with CF require repeated admission to hospital to treat respiratory complications; have poor quality of life and life expectancy; experience reduced aerobic fitness and physical functioning, and increased prevalence of anxiety and depression [2]. Higher levels of physical activity participation and aerobic fitness have been associated with improved health outcomes, in particular a slower decline in lung function [3], reduced need for hospitalization [4], and improved prognosis [5] in both children and adults with CF.

Regular participation in moderate-to-vigorous intensity physical activity (MVPA) has numerous health benefits including improved aerobic fitness and bone density, and reduced risk of depression [6]. Regular exercise and physical activity are recommended in CF treatment guidelines [2], to improve aerobic fitness; relieve breathlessness; and positively influence bone accretion, blood glucose control and clearance of pulmonary secretions [7, 8]. Despite the benefits of regular physical activity participation, people with CF demonstrate poor uptake and adherence to programs designed to augment physical activity and exercise [9]. This problem is compounded by the limited range of methods trialled to date to increase physical activity participation by people with CF [10].

Few strategies have been applied in the promotion of physical activity to people with CF. A Cochrane Review of strategies to promote physical activity participation by people with CF identified several studies which employed various forms of exercise training to improve physical activity, in mostly young people with mild CF lung disease [3, 10–13]. No study in the review investigated the effect of strategies such as motivational interviewing or the use of technology or telemedicine in promoting physical activity participation by people with CF. There is limited evidence that interventions of medium-longer term duration, with a requirement for self-directed participation, may be more effective than short-term, supervised training in improving physical activity participation [10].

Technology and telemedicine applications have the potential to create new ways to promote and support physical activity and exercise participation in this population, and are feasible and acceptable to people with CF [14, 15]. Importantly, no physical activity intervention study in people with CF to date has focussed on the period immediately post hospitalization. Objectively measured physical activity levels in adolescents and young adults with CF have been found to decline by over 50% in the first one month following hospital discharge [4]. In other populations with chronic respiratory disease, particularly people with chronic obstructive pulmonary disease (COPD), failure to recover physical activity levels in the month following hospital discharge is associated with an increased likelihood of hospital readmission [16]. Whether a web-based intervention to promote physical activity can effectively improve activity participation, and delay time to next admission, in young people with CF is unknown.

This paper describes the protocol for a randomized controlled trial testing a web-based application to promote physical activity in adolescents and young adults with CF. The aims of the trial are to: 1) investigate the effect of a web-based application (ActivOnline) to promote physical activity participation in young people with CF; 2) assess the effect of a technology based intervention (ActivOnline), in the period immediately following hospital discharge on aerobic fitness, lung function, quality of life, anxiety and depression, sleep quality, and healthcare utilisation in young people with CF. We hypothesise that the web-based intervention will improve uptake and participation in physical activity by young people with CF following a hospital admission for a respiratory exacerbation compared to usual care; that increased physical activity participation will lead to improvements in exercise capacity, lung function, quality of life, anxiety and depression, and sleep quality; and that healthcare utilization will be reduced in the intervention group over 12 months.

## Methods

### Design

A randomized, controlled, assessor-blinded trial will be conducted at eight Australian sites (Alfred Health, Monash Health and Royal Children’s Hospital, Victoria; Royal Hobart Hospital, Tasmania; Royal Prince Alfred Hospital, Westmead Hospital and Children’s Hospital at Westmead, New South Wales; Royal Adelaide Hospital, South Australia). The Human Research Ethics Committee at Alfred Health approved the study for all sites, and local governance approvals were obtained from all participating sites. The trial was registered at www.anzctr.org.au (ACTRN12617001009303) on July 13, 2017. This trial protocol employs our established methods with respect to randomization procedures, data integrity and management, trial safety monitoring and managing participant withdrawals [17].

### Participants and recruitment

Potential participants will be all individuals with CF admitted to hospital for a respiratory cause at the participating sites. To be eligible for inclusion participants will: 1) have a confirmed diagnosis of CF; 2) be aged 12–35 years (inclusive); and 3) have access to the internet via a computer or mobile device. Potential participants will be excluded if they: 1) have a severe co-morbidity limiting mobilisation or physical activity participation (e.g. orthopedic, cardiac or neurological condition); 2) have been the recipient of a lung transplant; 3) are pregnant; or 4) they (or their parents) are unable to provide informed consent.

### Randomisation

Participants will be randomly allocated (1:1) to ‘usual care’ or the ‘ActivOnline’ intervention. A computer-generated, block randomization scheme will be used with stratification for 1) site of recruitment – to allow for differences in local treatment practices including those related to usual prescription of exercise, and 2) whether or not the participant is enrolled in fulltime schooling (primary or secondary versus not in fulltime schooling) as the time of transition from secondary school to university or the workforce is a known time for decline in physical activity participation [18].

Sequence generation will be performed by an individual who is independent of the research team and randomization will occur using an online database. The randomization sequence will be concealed from investigators. Participants will be allocated to groups after completion of one week of physical activity monitoring immediately following discharge from hospital. Participants will not be blind to the intervention, however all outcomes will be measured by an independent assessor blind to group allocation. The flow of participants through the study will be reported according to the recommendations of the Consolidated Standard of Reporting Trials (CONSORT) [19].

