#### ActivOnline intervention

Participants randomized to the active intervention group will be given individualized access to the ActivOnline program (www.activonline.com.au) and encouraged to use this for the 12-week intervention period, to track their physical activity, set goals, and self-monitor progress. This will be in addition to usual care.

ActivOnline uses principles of motivational interviewing and cognitive behavioural strategies, with the aim of increasing opportunity and motivation for physical activity participation. It provides a secure portal for recording and reviewing physical activity and exercise participation details. ActivOnline is a mobile platform accessible from any internet browser across a variety of devices including tablets and smartphones. When logging into ActivOnline participants will be prompted to set weekly exercise and physical activity goals, as well as to record details of their physical activity or exercise sessions including total time and step count. To support recording of daily step count participants may use their own activity tracker (e.g. Fitbit) or mobile telephone. A pedometer (Yamax digiwalker SW500, Yamasa Tokei Keiki Co., Ltd., Tokyo, Japan) will be provided to participants on request. Data entered into ActivOnline are displayed in numerical and graphical form to allow visualization of progress over time (see Fig. 1). Participants can choose the frequency of use of ActivOnline, as data can be entered retrospectively. If no activity has been logged for three days, a standardized alert message will be issued by the ActivOnline program and emailed to the participant. Participants in the intervention group will also be able to communicate with research clinicians directly via the messaging system contained within ActivOnline about the trial or their clinical status, should they require. The number and nature of contacts via the messaging system will be recorded.

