#### Secondary outcomes

Self-reported physical activity participation will also be assessed using the Habitual Activity Estimation Scale (HAES), a validated subjective measure of physical activity participation in young people with CF [27]. Two measures of physical activity participation will allow for comparison between patient perception of activity intensity and objectively measured data.Aerobic fitness will be assessed using the Modified Shuttle Test (25 level version; MST-25) [28], an extension of a field test of aerobic capacity which is a reliable and valid measure of exercise capacity in adults and children with CF [29–31]. The MST-25 is a symptom-limited estimated assessment of peak aerobic capacity with distance covered the outcome of interest. It requires participants to walk, or run as necessary, around two markers over a 10-m course in time with a pre-recorded audio signal. Each level of the test lasts for one minute, with the speed increasing by 0.61 km/hr each minute. Participants cease the test when they feel they are no longer able to continue or when they fail to meet the course marker on two consecutive shuttles [29].Assessment of the reasons underlying participants decision to engage, or not engage, in physical exercise will be undertaken using the Behavioural Regulation in Exercise Questionnaire (BREQ-2) [32]. The BREQ-2 has been used in young people [33] and adults [34] with a variety of chronic medical and psychological conditions.Spirometry measures of forced expiratory volume in one second (FEV_1_) and forced vital capacity (FVC) will be reported. Spirometry measures will be conducted according to American Thoracic Society/ European Respiratory Society (ATS/ERS) standard procedures [35].Health-related quality of life (HRQoL) will be assessed using the revised edition of the Cystic Fibrosis Questionnaire (CFQ-R) [36]. The CFQ-R is a valid and reliable tool that provides a disease-specific measure of HRQoL [36].Anxiety and depression will be evaluated using the Hospital Anxiety and Depression Scale (HADS) [37] and the Center for Epidemiologic Studies -Depression (CES-D) scale [38]. These scales have been used in establishing the prevalence of anxiety and depression in young people and adults with CF [39].As exercise can positively impact both sleep and health outcomes, participants will complete the Pittsburgh Sleep Quality Index (PSQI) [40] self-report measure of sleep quality. The PSQI has been validated widely, and previously used in children and young adults with CF [41].Healthcare utilization will be documented from the medical record. Time to next hospital admission and the number of hospital days up to 12 months following completion of the intervention period will be reported.

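### The statement that every outcome is measured by a blinded assessor is wrong for six secondary questionnaires, on which the unblinded participant is the rater; the accelerometer primary outcome is not affected

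*Protocol article*

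**What the plan says.** The Randomisation section makes a claim about every outcome: "Participants will not be blind to the intervention, however all outcomes will be measured by an independent assessor blind to group allocation". The Methods part of the abstract says much the same without the word all, and names no exception: "Outcomes will be assessed by a blinded assessor at baseline, after completion of the intervention, and at 3-months followup".

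The Secondary outcomes section introduces one instrument in these words: "Self-reported physical activity participation will also be assessed using the Habitual Activity Estimation Scale (HAES), a validated subjective measure of physical activity participation". It gives the purpose of holding this next to accelerometry: "Two measures of physical activity participation will allow for comparison between patient perception of activity intensity and objectively measured data". The same section calls the PSQI a self-report measure that the participant fills in. It also lists the BREQ-2 (reasons for exercising or not), the CFQ-R (quality of life), and the HADS and CES-D (anxiety and depression).

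Under ActivOnline intervention, participants in that arm are prompted to set weekly goals and to "record details of their physical activity or exercise sessions including total time and step count". An automatic email follows three days without an entry. Under Usual care, the control arm receives guideline information and encouragement, and no logging is described.

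**The concern.** The blinding sentence concedes that participants know their allocation and then offers the blinded assessor as the counterweight for all outcomes. That counterweight works only where the assessor, a device or a record produces the value. For a self-report the participant produces it. An assessor who administers or scores the form cannot remove the participant's knowledge of allocation from the answers.

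What is at stake is how the questionnaire results may be interpreted. The Background hypothesises benefit on quality of life, anxiety and depression, and sleep quality, and each of these is measured by questionnaire. Taken at face value, the Randomisation section would credit a difference on those scales with a protection against bias that the design does not provide.

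HAES deserves separate mention because it asks about the behaviour that only one arm is prompted to log. Reporting could therefore shift between arms without a change in activity. The documents show neither that it would shift nor in which direction.

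**Working it through.** No figure in the plan depends on this point, so the check is mainly a comparison of sections.

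**Step 1. Who produces the rating for each outcome?**

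| Outcome | Source of the value | Basis in the protocol article | Blinded-assessor claim |
|---|---|---|---|
| MVPA (primary) | Accelerometer and software | Primary outcome | Tenable for processing |
| Spirometry | Supervised test | Secondary outcomes | Tenable |
| MST-25 | Observed distance | Secondary outcomes | Tenable for supervision |
| Healthcare utilisation | Medical record | Secondary outcomes | Tenable for extraction |
| HAES | Participant | Labelled self-reported and subjective | Not tenable |
| PSQI | Participant | Labelled self-report | Not tenable |
| BREQ-2 | Participant | Questionnaire on own motives; not labelled | Not tenable |
| CFQ-R | Participant | Quality-of-life questionnaire; not labelled | Not tenable |
| HADS | Participant | Symptom scale; not labelled | Not tenable |
| CES-D | Participant | Symptom scale; not labelled | Not tenable |

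Six instruments fall outside the claim: two by the protocol's own label and four by what they measure. Nothing in the article limits the Randomisation sentence to the first four rows.

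**Step 2. How much of the secondary set is affected?** The abstract names four secondary domains: aerobic fitness, quality of life, anxiety and depression, and sleep quality. Only aerobic fitness (MST-25) does not rest on a questionnaire, so 3 of 4 are affected.

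**Step 3. Is the sample size affected?** Inputs from Sample size: difference 20 min/day, SD 26, power 80%, alpha 0.05 (two-sided assumed), 1:1 allocation. The standardised difference is 20/26 = 0.769. The two-sample t-test solution is 27.52 per arm, rounded up to 28, so 2 × 28 = 56, with power 80.7%. Allowing for attrition, 56/0.75 = 74.7, rounded up to 75. Both stated figures reproduce, and neither depends on the blinding statement.

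**Step 4. Illustration only.** Suppose there is no true effect but a pure reporting bias of *d* SD on one scale, tested by an unadjusted two-sided t-test at 0.05 with *n* = 28 per arm. The test statistic is then non-central t with 2*n* − 2 = 54 degrees of freedom and non-centrality *d*√(*n*/2) = *d*√14 = 3.742*d*.

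| Assumed bias *d* (SD) | Non-centrality | Chance of p < 0.05 |
|---|---|---|
| 0.1 | 0.374 | 0.066 |
| 0.2 | 0.748 | 0.114 |
| 0.3 | 1.122 | 0.197 |
| 0.4 | 1.497 | 0.312 |

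The range of *d* is assumed; the documents give no value. The planned analysis is a linear mixed model controlling for centre and baseline values as required, not this t-test. The number evaluable on the questionnaires is also unknown, because 28 per arm is the requirement for the primary outcome. The table shows how sensitive an open-label scale of this size would be. It does not measure the wording error, and rewording would not change it.

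**The case against.** The strongest reply is that nothing is hidden. The same sentence says that participants are unblinded, the trial is described only as assessor-blinded, and HAES and PSQI are openly labelled self-report. Measured by could also be read as administered and scored by, and the abstract does not say all. Self-reported secondary outcomes in an open behavioural trial are a legitimate design choice.

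Much of this stands. It makes the fault an overstatement rather than concealment, and it gives no reason to drop any instrument. It does not rescue the word all. Administration and scoring are not where knowledge of allocation enters a self-report, and the sentence presents assessor blinding as the answer to unblinded participants.

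A reader might infer more than the documents support:

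- **That HAES will be biased between arms.** Bias is possible, but its direction and size are not given. Logging might equally make self-report more accurate. Participants are encouraged and prompted rather than required to log, and they choose how often to use the program.
- **That a pooled HAES-accelerometer analysis is planned.** The article says only that having two measures permits a "comparison between patient perception of activity intensity and objectively measured data". It states no time point, model or pooling across arms, and such detail may properly sit in the full protocol or analysis plan.
- **That HAES is meant to support the primary result.** The article sets HAES against the objective measure as perception and never proposes that use.
- **That the MST-25 is another instance.** Participants may stop when they feel unable to continue, but the test also ends when the marker is missed on two consecutive shuttles, and the distance covered is observed.

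**Conclusion.** The point holds as an error of statement. The Randomisation section claims a property for all outcomes that the design does not have for six secondary instruments, which underlie three of the abstract's four secondary domains. The contradiction is explicit for HAES and PSQI. For BREQ-2, CFQ-R, HADS and CES-D it rests on the assumption that they are completed in the usual way, as ratings by the participant.

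The consequence is limited to what can be concluded from the questionnaires. The accelerometer primary outcome and the sample size stand as they are. No amount of bias has been demonstrated, and the 7% to 31% range in the working is conditional on assumed biases. The correction is worth making because recruitment was still open when the article was written, so the interpretation of these scales can be settled before results are known.

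**What to change.** 1. In Randomisation, limit the blinded-assessor statement to accelerometer processing, spirometry, supervision of the MST-25 and medical-record extraction. Align the Methods part of the abstract.
2. In the same place, state that HAES, BREQ-2, CFQ-R, HADS, CES-D and PSQI are reported by participants who know their allocation.
3. State that between-arm differences on these six will be interpreted as open-label evidence. Because only the intervention arm is prompted to log activity, add that a HAES difference alone will not be taken as evidence of increased activity without accelerometer support.

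The change is to wording and interpretation only. It needs no new data, staff or participants and leaves every instrument in place. The downside is a weaker stated claim for the questionnaire outcomes.

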### Interventions

#### Usual care

Physical activity and exercise is routinely advised for all patients with CF [20, 21]. All participants will be provided with age-appropriate information regarding recommended guidelines for physical activity participation. Participants will be referred to a free online resource (http://www.nhs.uk/Livewell/fitness/Pages/physical-activity-guidelines-for-young-people.aspx) containing guidelines and information regarding amount and intensity of daily physical activity participation [6]. Physical activities which involve the use of large muscle groups continuously will be encouraged [3], as will the preferred activities of the participants [11].

